### Statistical analysis

Analyses will be performed according to the intention-to-treat (ITT) principle and will be statistically analyzed for all randomized participants. Missing data will be filled in using the multiple imputation method. Statistical analysis will be performed by the Chinese Cochrane Center, West China Hospital, Sichuan University, China and SAS software will be used for statistical analysis. Quantitative indicators are described using mean, standard deviation, median, 25th percentile and 75th percentile. Categorical indicators are described using frequencies and percentages. The normality of the data will be verified by the Kolmogorov–Smirnov test (K-S test). Equality of variance between observed variables will be verified by Levene's Test. Baseline data will be analyzed using chi-square or Fisher's exact test for categorical indicators and ANOVA or the Kruskal–Wallis H test for quantitative indicators.

The primary outcome will be analyzed by generalized linear mixed effects model. Fixed effects included group, age, COPD sub-type, and years of smoking; random effects included sub-center, time, and time × group interaction. Secondary outcomes will be analyzed using linear mixed effects models, with fixed and mixed effects containing the same variables as the primary outcome indicators.

We will include participants who completed no less than 80% of their treatments in the per-protocol set (PPS). Several sensitivity analyses will be conducted to examine the robustness of the finding. First, we will exclude the participants with acute exacerbations during treatment period. Second, we will exclude the participants who have infected COVID-19 during treatment period. We will analyze each of the subgroups that may potentially influence the outcomes, including: 1) Age: < 60 or > 60; 2) Smoking history: yes or no; 3) FEV1%pre: ≤ 50 or > 50; 4) Type of COPD: chronic bronchitis type or emphysema type. Statistical test will be a 2-sided test, with *P* < 0.05 considered statistically significant.

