#### Primary outcome

The primary outcome is the proportion of responders at week 12. Responder is defined as participants with a ≥ 4-unit decline in total SGRQ score compared with baseline. A decline of at least 4 points in the total SGRQ score has been determined to be the minimal clinically important difference (MCID) [32]. ≥ 4-unit worsening of SGRQ total score was associated with increased risk of death. The SGRQ is one of the most widely used scales for measuring health impairment and quality of life in adult patients with respiratory diseases, including 1. symptoms (frequency and severity of symptoms); 2. activity (ability to cause breathlessness or limitation of activity due to breathlessness); and 3. impact on daily activities (impairment of social competence and psychological impairment due to airway disease). The above 3 main aspects are scored according to the weights of different questions to obtain the symptom score, activity score and impact score, and finally, the total score is summarized. Higher patient scores indicate poorer quality of life [33]. SGRQ scores will be evaluated at weeks 0, 4, 8, and 12 of enrollment and every 3 months during the follow-up period.

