### Sample size calculation

As reported in previous studies [15, 41], the mean improvement in SGRQ was -7.1 for patients in the three times a week acupuncture group, the mean change in SGRQ was -2 for patients in the SA group, the mean change in SGRQ was -0.8 for patients in the blank control group, with a standard deviation of 14.2. Using a two-tailed test with a category 1 error of 0.05 and a statistical efficacy of 80%, a sample size of 88 cases per group was calculated, with a maximum of 20% of subjects allowed to drop out or disengage for a required sample size of 110 cases per group. The once a week and twice a week acupuncture groups were set up with the same sample size as the three times a week acupuncture groups, and a total of 550 subjects were included.

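### Neither the primary nor the secondary models adjust for the baseline value of the outcome, so precision is lost in a trial already short of power for its primary comparison with sham

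*Protocol article*

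**What the plan says.** The Statistical analysis section specifies a generalized linear mixed model for the primary outcome: "Fixed effects included group, age, COPD sub-type, and years of smoking", with sub-center, time and the interaction of time with group as random effects. The secondary outcomes get linear mixed models, "with fixed and mixed effects containing the same variables as the primary outcome indicators". No baseline value of any outcome appears in either specification.

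The outcomes depend on baseline by definition. Under Primary outcome: "Responder is defined as participants with a ≥ 4-unit decline in total SGRQ score compared with baseline". Under Secondary outcomes, items 2 to 7 (SGRQ, mMRC, CAT, lung function, 6-minute walk distance, SF-36) are each labelled as a change, and item 1 is the same responder definition at week 64.

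The baseline values are available: "SGRQ scores will be evaluated at weeks 0, 4, 8, and 12 of enrollment". The Secondary outcomes section gives week-0 assessments for mMRC, CAT, SF-36, lung function and walk distance as well.

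**The concern.** A change score is follow-up minus baseline, so measurement error and regression to the mean tie it to its own baseline. On a bounded scale such as the SGRQ there is also a floor: a patient who starts low has less room to fall by 4 points. Baseline is therefore a covariate that bears directly on both the change and the responder status derived from it. Nothing in the protocol suggests that age, COPD sub-type or years of smoking would capture this.

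Two things are at stake. A chance difference in baseline between arms carries through to responder rates and mean changes, with nothing in the model to correct it. And precision is given up at no saving, in a trial that on its own planning figures has less than 80% power for its primary outcome against sham.

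**Working it through.** **Inputs.** From Sample size calculation: mean SGRQ change -7.1 (three times a week), -2 (sham), -0.8 (waiting list); SD 14.2; two-sided 0.05; 80% power; 88 per group, 110 after 20% dropout. From Primary outcome: responder cut at a fall of 4 units. Assumed, because the protocol does not give it: the correlation r between baseline and change, taken as -0.3 to -0.5. Change scores are also assumed normal.

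**1. The plan's own figure.** The 88 reproduces as a three-group one-way ANOVA on mean change. The grand mean is -3.3 and the squared deviations are 14.44 + 1.69 + 6.25 = 22.38. The noncentrality at n = 88 is 88 × 22.38 / 14.2² = 9.77. Power is 0.796 at 87 and 0.801 at 88. Then 88 / 0.8 = 110, and 5 × 110 = 550. The arithmetic is sound, but it concerns an omnibus test on means, not the responder proportion.

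**2. Power for the actual primary outcome.** P(change ≤ -4) = Φ((-4 - mean)/14.2):

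- three times a week: Φ(3.1/14.2) = 58.6%
- sham: Φ(-2/14.2) = 44.4%
- waiting list: Φ(-3.2/14.2) = 41.1%

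For 58.6% against 44.4% at 88 per arm, the two-proportion test has power Φ((0.1424 - 1.96 × 0.0753)/0.0746) = 0.47. With all 110 it is 0.56, and 80% needs 193 per arm. Against waiting list, power at 88 is 0.65.

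**3. What the assumed r means.** With equal variances at baseline and week 12, r = -√((1 - ρ)/2), where ρ is the baseline to week-12 correlation. So r = -0.3, -0.4, -0.5 corresponds to ρ = 0.82, 0.68, 0.50. Under that condition r is zero only if ρ = 1.

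**4. Responder outcome.** Simulated two-arm trials against sham, 88 per arm, logistic model without and with baseline SGRQ (6,000 per setting):

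| r | power without | power with | gain in effective n |
|---|---|---|---|
| -0.3 | 0.451 | 0.492 | 6% |
| -0.4 | 0.461 | 0.511 | 10% |
| -0.5 | 0.448 | 0.538 | 18% |

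A repeat with 8,000 trials per setting gives 0.464 to 0.502, 0.468 to 0.515 and 0.447 to 0.525. The squared ratio of the mean test statistics gives gains of 5%, 10% and 17%, in line with the last column. Converting the tabulated powers instead, by ((1.96 + z_with)/(1.96 + z_without))² - 1 with z the normal quantile of the power, gives 12%, 14% and 26%. That route is more sensitive to simulation error, so the smaller figures are used.

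A separate simulation set by ρ gives power with baseline of 0.57, 0.54, 0.51 and 0.48 against sham for ρ = 0.3, 0.5, 0.7, 0.8, from 0.45-0.47 without. Against waiting list it gives 0.75, 0.72, 0.70 and 0.68, from 0.63-0.65.

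**5. Continuous change scores.** Adjusting for baseline multiplies the residual variance by 1 - r², which equals (1 + ρ)/2. The gain in effective n is 1/(1 - r²) - 1: 10%, 19% and 33% for r = -0.3, -0.4, -0.5. At ρ = 0.5 the SGRQ comparison with sham needs 92 per arm instead of 122, and power at 88 rises from 0.66 to 0.79.

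**6. Chance imbalance.** A baseline difference of one standard error shifts the unadjusted difference in mean change by |r| × 14.2 × √(2/88). That is 0.64 units at r = -0.3 and 1.07 at r = -0.5, or 13% and 21% of the planned 5.1.

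**The case against.** The best case against is that this is a choice about precision, not an error. Randomization is stratified by center, center is in the model, and the comparison is valid without baseline. Chance imbalance is already covered by the nominal error rate. That is right, and it is why the point is not a validity failure.

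The covariate sentence may not be exhaustive in a condensed article. But it names specific covariates, and the secondary models are tied to the same list. Even if more were intended, the baseline term should be named.

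A linear mixed model that keeps week 0 as a repeated response would bring baseline in through the covariance. The protocol names change as the secondary outcome and does not describe such a model. The route is closed for the primary outcome, because responder status does not exist at week 0.

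The size of the gain depends on an undocumented correlation. At r = -0.2 (ρ = 0.92) power rises only from about 45% to 48%, and the continuous gain is about 4%. The simulations use 88 per arm and leave out age, sub-type and smoking; if those correlate with baseline SGRQ, the extra gain is smaller. With 110 per arm and no missing data, power goes from about 56% to 58% (r = -0.3) or 64% (r = -0.5). These points limit the size. The gain remained positive in every setting tried.

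The adjusted odds ratio is conditional on baseline. The planned one is already conditional on age, sub-type, smoking years and center, so this affects its interpretation but is no reason to omit the term.

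**Conclusion.** The concern holds. The stated models omit the baseline value of the outcome, although responder status and six secondary outcomes are defined by change and the baseline values are collected. At 88 per arm, adding baseline SGRQ raises responder power against sham from about 45-46% to 49-54%, worth about 6-18% more patients. For continuous change scores the gain is 10-33%. Both ranges rest on an assumed baseline-change correlation of -0.3 to -0.5, equal variances over time and normal scores; a weaker correlation gives less.

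The omission costs precision and leaves chance imbalance uncorrected; it does not bias the comparison. Nor does adjustment rescue the power. The shortfall comes from sizing the trial on mean change while the primary outcome is a proportion, and the comparison with sham stays well below 80% either way. The exacerbation count is not a change score and is outside this point. This should be changed, but it does not threaten the validity of the trial.

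**What to change.** Add baseline SGRQ total score, as a continuous fixed covariate, to the primary responder model; the week-64 responder analysis needs the same term. In each change-from-baseline model, add the baseline value of that same outcome. If the intention is to keep week 0 as a repeated response in the linear models, say so explicitly; that serves the same purpose for those outcomes but not for responder status.

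The change should be fixed in the analysis plan before unblinding. It needs no new data and no extra visits. The one consequence to state is that the reported odds ratio is then also conditional on baseline SGRQ.

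### The primary model lists time and time × group as random effects, so the week-12 group difference is not a fixed, testable parameter; how a participant's repeated visits are correlated should also be stated.

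*Protocol article*

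**What the plan says.** Under Primary outcome, the article names one time point: "The primary outcome is the proportion of responders at week 12". A responder is a participant whose total SGRQ score has fallen by at least 4 units from baseline. The same section sets repeated measurement: "SGRQ scores will be evaluated at weeks 0, 4, 8, and 12 of enrollment and every 3 months during the follow-up period". With 52 weeks of follow-up (Study design), that is three post-baseline visits up to week 12 and seven up to week 64.

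Under Statistical analysis: "The primary outcome will be analyzed by generalized linear mixed effects model". The terms are then listed. Fixed part: "Fixed effects included group, age, COPD sub-type, and years of smoking". Random part: "random effects included sub-center, time, and time × group interaction". Secondary outcomes get linear mixed models "with fixed and mixed effects containing the same variables as the primary outcome indicators". The article does not say which visits enter the primary model, and it mentions no participant effect or residual covariance.

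**The concern.** The question is the difference between groups at week 12. In a repeated-measures model, that difference is the group effect plus the group × time effect at week 12, and both must be fixed if the sum is to be estimated and tested. Here the second piece is random. It is assumed to average zero over visits, it is pulled toward zero, and no hypothesis test attaches to it. The group coefficient that remains describes the average visit. If the effect of acupuncture grows over 12 weeks, the average understates the week-12 effect. If the effect fades over follow-up and those visits are included, the average is diluted from the other end.

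A second question is precision. None of the listed random effects is indexed by participant. If nothing else in the model links a participant's visits, they count as independent given center, time and time × group, and the standard error of the group difference is too small whenever a person's responses are positively correlated. Positive correlation is likely, because every response is a change from the same baseline score.

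Both questions carry over to the secondary outcomes, which inherit the same terms.

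**Working it through.** **The plan's own figure.** The Sample size calculation section gives mean SGRQ changes of -7.1 (three times a week), -2 (sham) and -0.8 (waiting list), SD 14.2, two-sided alpha 0.05 and 80% power. A three-group one-way ANOVA on these values has power 0.796 at 87 per group and 0.801 at 88, so 88 per group is reproduced; 88 / 0.8 = 110, and 5 × 110 = 550. The present point does not depend on this figure, but the means and SD are used below.

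**Step 1: what the group coefficient targets.** Assume that change is normal with SD 14.2 at each visit. P(responder) = Φ((-4 - mean) / 14.2).
- Week 12, three times a week: Φ(3.1 / 14.2) = 0.586.
- Week 12, sham: Φ(-2 / 14.2) = 0.444.
- Week-12 difference: 0.142 (log odds ratio 0.574).

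The article does not give the time course of the effect, so three are shown:

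| Share of final change at weeks 4, 8, 12 | Difference by visit | Visit average | Week 12 |
|---|---|---|---|
| 1/3, 2/3, 1 | 0.047, 0.095, 0.142 | 0.095 | 0.142 |
| 1/2, 3/4, 1 | 0.071, 0.107, 0.142 | 0.107 | 0.142 |
| 1, 1, 1 | 0.142, 0.142, 0.142 | 0.142 | 0.142 |

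With linear build-up the target is a third too low: (0.142 - 0.095) / 0.142 = 0.33. On the log odds scale it is 0.383 against 0.574. The two targets agree only if the effect is complete by week 4 and stays constant.

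**Step 2: precision if no within-participant covariance is specified.** The within-person correlation is not in the article and is assumed. The simulation is under no effect: 5 arms of 110, responder rate 0.444, 4,000 runs per setting. The model is a balanced linear approximation to the written one (fixed group, random time and time × group, no participant effect), without covariates or center. Type I error is for a nominal 5% comparison of two arms, with a normal critical value and with a t value on (5 - 1) × (3 - 1) = 8 degrees of freedom. The binary correlations are approximate, read from one simulated data set per setting.

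| Latent correlation (binary, about) | Model SE | True SD | Type I, normal | Type I, t on 8 df |
|---|---|---|---|---|
| 0 | 0.042 | 0.039 | 0.041 | 0.016 |
| 0.3 (0.18) | 0.040 | 0.045 | 0.084 | 0.039 |
| 0.5 (0.35) | 0.039 | 0.050 | 0.124 | 0.068 |
| 0.7 (0.49) | 0.039 | 0.055 | 0.171 | 0.106 |
| 0.85 (0.63) | 0.039 | 0.059 | 0.197 | 0.126 |

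Across the positively correlated settings, three visits give about 4% to 20%. With the participant as the unit, the same data give 0.044 to 0.055; a week-12-only comparison gives 0.040 to 0.050.

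Cross-check by design effect, 1 + (T - 1)ρ with T = 3: ρ = 0.5 gives 2.0, an SE ratio of 1/√2 = 0.707, and a type I error of 2 × (1 - Φ(1.96 / √2)) = 0.166. This is close to the simulated 0.171 at a binary correlation of 0.49. The random time × group term does not absorb the problem, because variation between participants is shared across visits and enters the group means, not the interaction.

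If all seven post-baseline visits entered the model, latent correlations of 0.5 and 0.7 would give 0.26 and 0.32 with normal critical values, or 0.24 and 0.29 with t values.

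**The case against.** The strongest objection concerns the participant term. A journal article condenses the plan. Its list of random effects is not declared complete, and in SAS, the named software, correlation within a participant is often set through a residual covariance structure that would not appear in such a list. The analysis plan that might name it is not shown. This stands: the article does not establish that the trial will analyze repeated visits as independent.

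A reader might also infer that standard errors are about 30% too small, or that the false-positive rate reaches 25% or more. The documents do not support either as a headline. The 30% needs a binary correlation near 0.5; at 0.33 the design effect is 1 + 2 × 0.33 = 1.67, and the standard error is about 23% too small. The larger error rates require follow-up visits to enter the week-12 model. The article does not say that they do, and it lists response at week 64 as a separate secondary outcome.

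It can also be said that a week-12 contrast is still available, as the fixed group effect plus predicted random deviations. That is true, but the prediction is shrunken and is not the tested parameter, so it is a poor basis for a primary analysis.

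Two readings might rescue the model terms, and neither does. If time means a slope for each participant, the precision problem eases, but there is still no fixed group × time term to give a week-12 contrast. If only week-12 data enter, precision is not at issue, but the listed time terms then have no meaning.

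**Conclusion.** The point holds on the estimated quantity, with high confidence. Placing time × group in the random part is a stated choice, and it does not match an outcome fixed at week 12. The size of the mismatch depends on the unknown time course: none if the effect is immediate and constant, and about 0.095 against 0.142 under linear build-up with the article's own means and SD.

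On precision the conclusion is conditional, with moderate confidence. If no within-participant covariance is specified anywhere, three post-baseline visits give a type I error of roughly 4% to 20%, and more if follow-up visits are included. That range rests on assumed correlations, on the choice of degrees of freedom and on a linear approximation to the model. With zero correlation there is no inflation. This part asks for a statement in the plan; it is not a demonstrated error.

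**What to change.** Rewrite the model specification before any unblinded analysis, in one of two ways.

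1. Repeated-measures model: put visit and group × visit in the fixed part with group and the listed covariates. Include a participant random effect or a within-participant covariance structure, keep sub-center, state which visits enter, and name the week-12 group contrast as the primary estimate.
2. Single-visit model: fit a logistic mixed model to week-12 responder status, with a sub-center random intercept and no time terms.

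Apply the same correction to the secondary models, naming the time point of each contrast. If the analysis plan already specifies a within-participant covariance, citing it settles the precision question. Adding baseline SGRQ as a covariate would be a reasonable improvement but is optional and not part of this error.

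The cost is wording in the protocol and analysis plan. No new data or visits are needed.

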#### Secondary outcomes

Secondary outcomes included the following eight items: 1) the proportion of responders at week 64; 2) change in the SGRQ Scale; 3) change in the mMRC Scale; 4) change in the CAT Scale; 5) change in the Lung Function Screening Indicators (including FEV1, FEV1%pre, FVC and FEV1/FVC); 6) change in the 6MWD;7) change in SF-36 Scale; 8) the number of moderate and severe acute exacerbations during the follow-up period.

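### One linear mixed model is prescribed for every secondary outcome, although week-64 responder status is binary and the exacerbation number is a count

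*Protocol article*

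**What the plan says.** All references are to the protocol article.

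- Statistical analysis, primary outcome: "The primary outcome will be analyzed by generalized linear mixed effects model".
- Statistical analysis, next on secondary outcomes: "Secondary outcomes will be analyzed using linear mixed effects models", with the model terms carried over from the primary outcome. No exception is made by outcome type, and no other method is named for binary or count outcomes.
- Primary outcome: "Responder is defined as participants with a ≥ 4-unit decline in total SGRQ score compared with baseline". Responder status is therefore yes or no for each participant at any visit.
- Secondary outcomes, first item: "1) the proportion of responders at week 64". Last item: "8) the number of moderate and severe acute exacerbations during the follow-up period". The six items between them are changes in scales or measurements.
- The description of the measures after that list has exacerbations assessed at weeks 0, 4, 8 and 12 and every three months in follow-up. It also says they will be counted over the year after treatment ends.
- Statistical analysis also plans intention-to-treat analysis of all randomized participants with multiple imputation. Sample size calculation allows up to 20% drop-out.

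**The concern.** A linear mixed model assumes a continuous response with normal errors of constant variance, and it reports a mean difference. Neither a yes/no status nor an event count has that form. This is not a detail left to a statistical analysis plan, because the article names a model and the model does not suit two of the outcomes it covers. The article is also inconsistent with itself: it treats responder status as needing a generalized model at week 12 and a linear one at week 64.

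The 52-week follow-up is there to show whether an effect lasts. The week-12 and week-64 responder results will be read side by side, so they should come from the same model on the same scale. For exacerbations, the usual summary is a ratio of rates per unit of follow-up time, and the stated model does not provide one.

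**Working it through.** **Step 1. Match outcomes to models.**

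| Outcome | Type | Model stated |
|---|---|---|
| Responder, week 12 (primary) | binary | generalized linear mixed |
| Responder, week 64 | same binary variable | linear mixed |
| Changes in SGRQ, mMRC, CAT, lung function, 6-MWD, SF-36 | change scores or measurements | linear mixed |
| Number of moderate and severe exacerbations | count | linear mixed |

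The second and last rows are the mismatches. The plan gives no figure specific to this point, so there is none to reproduce. The steps below only gauge the consequences.

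**Step 2. Responder scale.** Inputs from Sample size calculation: mean SGRQ change -7.1 (three times a week) and -2 (sham), SD 14.2. Assumption: changes are normal and these means apply at both visits. The responder probability is Φ((-4 − mean)/14.2).

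- Three times a week: Φ(3.1/14.2) = 0.5864
- Sham: Φ(−2/14.2) = 0.4440
- Risk difference: 0.5864 − 0.4440 = 0.1424
- Odds ratio: (0.5864/0.4136)/(0.4440/0.5560) = 1.78

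The article does not state the week-12 link. With the usual logit, the same pair of proportions would appear as an odds ratio of 1.78 at week 12 and as a difference of 14.2 percentage points at week 64. The variances p(1 − p) are 0.2425 and 0.2469, almost equal. At proportions like these the constant-variance assumption does little harm, and the problem is the change of scale and model.

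**Step 3. Count model.** The article gives no exacerbation rate, variance or share of zeros, so every input here is assumed: control rate μ of 0.5, 1.0 or 1.5 per year, negative binomial dispersion 1, rate ratio 0.7, and complete follow-up. The 88 per arm is the plan's figure before the drop-out allowance. The variance is μ + μ², and the probability of zero events is 1/(1 + μ).

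| μ control | P(zero), control | Variance, control / treated | Ratio |
|---|---|---|---|
| 0.5 | 0.67 | 0.75 / 0.4725 | 1.59 |
| 1.0 | 0.50 | 2.00 / 1.19 | 1.68 |
| 1.5 | 0.40 | 3.75 / 2.1525 | 1.74 |

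Under these assumptions the variance changes with the mean, so constant variance fails whenever the arms differ.

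**Step 4. Does that distort the test?** Two-arm simulation, 1,500 replicates per setting, t test against a negative binomial model given the true dispersion. Rejection rates at 0.05:

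| μ control | No effect: Gaussian / neg. binomial | Rate ratio 0.7: Gaussian / neg. binomial |
|---|---|---|
| 0.5 | 0.043 / 0.039 | 0.251 / 0.250 |
| 1.0 | 0.047 / 0.045 | 0.359 / 0.360 |
| 1.5 | 0.054 / 0.057 | 0.426 / 0.430 |

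The Monte Carlo standard error at 0.05 is √(0.05 × 0.95/1500) = 0.006, so both tests are close to nominal and their power is practically the same. The simulation covers a simple comparison without drop-out, not the full mixed model.

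**The case against.** The strongest defence is that the stated model would still give usable answers. A linear model for a binary outcome estimates a risk difference, which is valid enough with robust standard errors, and a week-12 risk difference can be derived from a logistic model. This stands, so the two visits are inconsistently modelled rather than impossible to compare.

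Four stronger readings are tempting, and the documents do not support them.

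- **Standard errors for the count are poor.** A reader might infer this from skewness, but the simulation does not show it.
- **The time terms cannot be fitted because there is one total per participant.** A single annual total is one reading. Exacerbations are also assessed every three months, so interval counts could be modelled over time. They would still be counts.
- **The analysis is biased whenever drop-out differs between arms.** For example, assume 20% against 10% drop-out with leavers lost halfway. Observed person-time is then 1 − 0.2 × 0.5 = 0.90 against 1 − 0.1 × 0.5 = 0.95, a gap of about 5%. That carries into the result only if partial counts are used as full-year totals. The plan does not say so, and its multiple imputation points the other way. What stands is that the stated model has no term for time at risk.
- **The counts are overdispersed with many zeros.** This may be so, but the article gives no rates, and entry requires at least one moderate or severe exacerbation in the past year, which selects for events. It remains an assumption.

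One could also say that the article is shorthand and a fuller plan may differ. No such plan is shown, and the sentence as published names one model for all secondary outcomes.

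**Conclusion.** The point holds as a misspecified and internally inconsistent choice of model for two of eight secondary outcomes. That part rests on the text alone and needs no assumption. What suffers is the model form, the effect measure and the consistency between weeks 12 and 64. With assumed rates of 0.5 to 1.5 per year and dispersion 1, the effect on type I error and power in a simple comparison is negligible, so the trial's conclusions are not shown to be at risk. It is still worth correcting: the mismatch is explicit, the correction is cheap, and a model changed after the data are seen could look data-driven.

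**What to change.** Reword the secondary-outcome sentence in Statistical analysis as follows.

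- **Linear mixed model:** only for the continuous change outcomes. mMRC has five grades, so say whether its change is analysed as a score or with an ordinal model.
- **Week-64 responders:** the same generalized (binomial) mixed model as week 12, with the link stated. Ideally fit one longitudinal model and take the week-12 and week-64 contrasts from it.
- **Exacerbations:** a negative binomial (or Poisson) log-link model with log follow-up time as offset, sub-center and the covariates already planned (age, COPD sub-type, years of smoking), reporting a rate ratio. If three-monthly interval counts are used, fit the mixed-model version with time and time × group. Prior-year exacerbations could be added as a covariate but are not needed to correct the error.
- **Incomplete follow-up:** say whether partly observed counts enter through the offset or are completed by imputation, so that the offset and the imputation rule do not conflict.

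The cost is a wording change in the analysis section, best made before unblinding. It needs no extra data, visits or participants.
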